### Outcome variables

#### Primary

The primary efficacy outcome is the sacral and ischial pressure injury score measured over time.

#### Secondary

Secondary outcomes are time to event endpoints (time to resolution of ulcer, time to worsening of ulcer, time to discharge alive, daily subjective evaluation of ulcer, and mortality).

#### Exploratory

Our first exploratory endpoint will be total hospital cost effectiveness analysis within a subset of the patients. We will measure incremental cost-effectiveness ratios (ICERS) between traditional care and IES interventions of each procedure for the treatment of pressure ulcers, done within a subset of the patients. Furthermore, patient experience with respect to sleep disturbance, distraction or discomfort, and feeling of electric shock will be assessed with a daily questionnaire. Daily assessment of the device area with respect to redness or skin issues will similarly be documented with a daily questionnaire (Additional file 3). The assessors will be research personnel.

### Data collection and management

Data for wound assessment is collected by the electronic medical record as is all other baseline and study data as specified in the case report form (CRF) (Additional file 2). When able, data will be automatically extracted from the EMR. Study personnel at the participating sites record data on CRFs and submit the CRFs through a secure web-based computerized database (i.e., iDataFax). Patients are identified using a unique numeric code, and all patient data are anonymized to ensure patient confidentiality. Data validity checks are programmed in the database and are monitored by data management assistants from the Project Office through multi-level data validation of CRFs.

To promote participant retention and complete follow-up, all data per the protocol will continue to be gathered from the participant as part of the modified intention to treat analysis (i.e., including all randomized patients who receive at least part of the study intervention) should they disenroll unless they request that subsequent data not be gathered. If a patient withdraws from study and also withdraws consent for disclosure of future information, no further evaluations are performed, and no additional data is collected. The sponsor may retain and continue to use any data collected before the withdrawal of consent.

## Statistical methods

### Data analysis

#### Analysis population

All randomized participants who have received any of the study intervention will be included in the primary endpoint analysis using modified intention-to-treat (mITT). The mITT data will be used to evaluate efficacy on the primary and secondary endpoints, and this data will comprise the analysis population.

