## Methods

### Trial design

PROTECT-2 is a parallel-group, unblinded multi-center randomized clinical trial that will assess whether IES combined with the standard of care (treatment) is superior to the standard of care alone (control). The trial is already IRB approved at all trial sites (US, Austria) and registered at ClinicalTrials.gov (NCT05085288). The SPIRIT checklist and figure for our proposal is provided in Fig. 1 and additional file 1. [12].

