### Randomization and blinding

Randomization sequences will be generated using the PLAN procedure in the SAS statistical software and will be stratified by clinical site and initial pressure injury stage at point of consent (stage I or II). Furthermore, random sized blocks will be used. Study personnel will randomize patients after enrollment via a central 24-h Interactive Web Randomization System (REDCap). This is an open label study, so no blinding is required. Randomization codes will be maintained until after all the data are collected and analyzed. The patient and study staff will be informed of the randomized allocation.

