**Fig. 2 Fig2:**
[figure not shown]
The IES system. Electrodes are placed directly on the skin overlying the gluteal muscles but not directly on the pressure ulcer

The device produces charged pulses at 30 Hz. Stimulation intensity is progressively increased until visible muscle contractions of the gluteus maximus muscles are seen, up to a maximum current of 100 mA. Stimulation occurs for 10 s every 10 min. Chosen device parameters approximate those shown to induce pressure redistribution and sustained elevation in tissue oxygenation based on previous studies. Each subject will receive IES consistently 24 h a day from entry and while in the ICU except for brief periods necessary for particular tasks in patient care (ex. dressing changes, operating room needs). While in non-ICU environments, the device will be used while in bed and not participating in physical therapy, mobilization, toileting, and similar activities where no consistent pressure in applied to the sacral area. The study device will be used until discharge, death, patient or LAR request for disenrollment, or the need for surgical or other interventions that preclude the use of IES. Should patients request not to have the study device for a short period of time, this will be notated and they remain in the trial group. If there are patient concerns about contextual use of the device, such as toileting or sleeping, these are discussed with the patient, and should the patient not have the device on per the protocol, this will be noted in the twice daily assessments. If there are medical interventions that require that the sacrum and ischium not be examined, such as unstable open-chested patients, short-term pausing is acceptable and will be documented on the case report form (Additional file 2). If these interventions are longer term or if the patient develops any condition not conducive to the use of the trial device, the device will be discontinued until these conditions are resolved. Research personnel will visit each subject in the study group Monday through Friday to administer a questionnaire to the bedside nurse, ensure proper use of the device, and address participant concerns.

Subjects in the intervention group will receive all other wound care preventatives and treatments that are standard of care. No standard interventions for wound care treatment are prohibited. The standard of care comparator is to isolate the effect of IES in addition to what is the current standard of care.

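### The only efficacy population leaves out patients who never start study treatment, a rule that in this open-label trial can in practice remove patients from the IES arm alone

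*Protocol article*

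**What the plan says.** The rule appears twice in the protocol article. *Analysis population* states: "All randomized participants who have received any of the study intervention will be included in the primary endpoint analysis using modified intention-to-treat (mITT". *Data collection and management* glosses modified intention-to-treat as "including all randomized patients who receive at least part of the study intervention".

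No other set is offered for efficacy: "The mITT data will be used to evaluate efficacy on the primary and secondary endpoints, and this data will comprise the analysis population". The alternative models and sensitivity analyses (GEE, recurrent time-to-event) change the model, not the patients.

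*Trial design* defines the comparison as whether "IES combined with the standard of care (treatment) is superior to the standard of care alone (control". The device section under *Trial intervention* adds: "The standard of care comparator is to isolate the effect of IES in addition to what is the current standard of care". *Randomization and blinding* says "This is an open label study, so no blinding is required" and "The patient and study staff will be informed of the randomized allocation". Besides discharge and death, the device section lists as reasons for ending device use "patient or LAR request for disenrollment, or the need for surgical or other interventions that preclude the use of IES".

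**The concern.** Whether a patient has received any of the study intervention is settled after randomization. In a blinded trial with a sham device the condition might act alike in both arms. Here it cannot, because the arms differ only by an added device and allocation is open.

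An IES patient who refuses the device on learning the allocation, or who is discharged, dies or needs a precluding intervention before first use, leaves the analysis. A control patient with the same course stays. If such patients have a different ulcer prognosis from the rest, the arms are no longer comparable, and an apparent effect can arise, or a real one shrink, without the device having done anything. The rule governs the primary endpoint, the secondary endpoints and, through the primary outcome, the interim looks for efficacy and futility.

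**Working it through.** **Who can be excluded.** The article does not define the study intervention for control patients, so there are two readings.

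- Taken to mean IES, the rule would remove the whole control arm, which cannot be intended.
- Taken to mean the assigned care, a control inpatient qualifies at once through routine wound care. An IES patient may also qualify through routine care, in which case nobody is excluded and the condition has no purpose.

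The workable reading is that a patient is excluded by never starting the device. A control patient lost immediately after randomization is a theoretical exception.

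**The plan's own figure.** The sample size is not in dispute. For Table 1(A), the tie-corrected Wilcoxon formula is N = (1.960 + 1.282)² × (1 − Σp̄³) / [3(P − 0.5)²]. With P = 0.55625 and Σp̄³ = 0.468 it gives about 589, against 586 stated. Taking the stated 668 with interim looks, 668 × [1 + 9 × 0.8]/10 = 547.8, the stated 548 (274 per arm).

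**Illustrative bias.** Inputs:

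- 72.5% at score 0, the control row of Table 1(A), which is itself hypothetical, applied to both full arms so that there is no true effect;
- f, the share of the IES arm never started, *assumed* 2%, 5% or 10% (about 5, 14 or 27 of 274);
- q, the share of those patients reaching score 0, *assumed*.

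The retained IES arm then has r = (0.725 − f·q)/(1 − f) at score 0, and the spurious difference is r − 0.725.

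| f | q = 50% | q = 72.5% | q = 90% |
|---|---|---|---|
| 2% | 0.715/0.98 = 72.96%: **+0.5** | 0 | 0.707/0.98 = 72.14%: **−0.4** |
| 5% | 0.700/0.95 = 73.68%: **+1.2** | 0 | 0.680/0.95 = 71.58%: **−0.9** |
| 10% | 0.675/0.90 = 75.00%: **+2.5** | 0 | 0.635/0.90 = 70.56%: **−1.9** |

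Bold entries are percentage points in favour of (+) or against (−) IES. Table 1(A) targets 82.5 − 72.5 = 10 points, so the q = 50% column is about 5%, 12% and 25% of the target.

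**Illustrative type I error at q = 50%.** The standard error at which 10 points has 90% power is 10/(1.960 + 1.282) = 3.085 points. The shifts are 0.149, 0.384 and 0.810 standard errors. Two-sided error is 1 − Φ(1.960 − shift) + Φ(−1.960 − shift), or about 5.3%, 6.7% and 12.8% against a nominal 5%. This is a fixed-sample approximation on one binary cut, not the planned repeated-measures cumulative logit model.

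**The case against.** The rule is narrow. One use of the device is enough to stay in, and IES is meant to run from entry, so the window for never starting is short. The device section keeps patients who ask for a short break in their group, and data collection continues after disenrollment unless consent for it is withdrawn. All of this stands: the rule does not drop patients who stop early or use the device poorly. None of it protects a patient who never starts.

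Several stronger readings are tempting and are not supported.

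- *Patients in whom no contraction can be produced are dropped.* Current is raised until contraction is seen, so such a patient has been stimulated and has arguably received some of the intervention.
- *Every excluded patient has outcome data anyway.* Wound scores do come from the medical record. However, a patient discharged before set-up would have few or none, since scores after discharge are used only if available, and a patient who withdraws consent for further data has none from then on.
- *Never-starters are known to have a worse prognosis, so the rule favours IES.* The article reports neither how many there are nor how they fare. Early discharges could be healthier, which reverses the sign.
- *The benefit of randomization is lost outright.* The loss depends on the number of never-starters. With none, the two sets coincide.

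A statistical analysis plan not shown here might add an all-randomized sensitivity analysis. That would help, but the primary set fixed in this article would remain as it is.

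**Conclusion.** The point holds in this form: the stated efficacy population rests on a condition met after randomization that, in practice, only IES patients can fail, with allocation known, and no all-randomized analysis is named. That much follows from the text.

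That the exclusion biases the result is a possibility, not a demonstrated fact. Its size and sign depend on the never-start rate and on the prognosis of those patients, neither of which is documented. Under the assumptions above it runs from -1.9 to +2.5 points on a 10-point target, and is zero if never-starters have average prognosis. A reader might infer that the trial is set up to favour IES; the documents do not support that.

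**What to change.** Define the primary population, for primary and secondary endpoints, as all randomized patients analysed in the arm to which they were allocated, using every score available within the limits of consent. Keep the present set as a sensitivity analysis, state what receiving the intervention means in each arm, and report the number never started by arm with reasons.

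The article reports 176 patients recruited by 30 December 2023 and a first interim analysis expected in January 2024. The change should therefore be made without reference to unblinded interim results, and its date recorded.

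The cost is a protocol amendment with ethics approval and a registry update where relevant, plus some dilution. If never-starters gain nothing and starters gain the planned 10 points, the all-randomized difference is 10 × (1 − f): 9.8, 9.5 or 9.0 points at 2%, 5% or 10%. With the standard error above, approximate power is Φ(3.242 × (1 − f) − 1.960), or 89%, 87% or 83% instead of 90%. The population change alone does not require a new sample size. If the never-start rate proves to be near the top of this range, the dilution deserves a look.

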#### Significance level

The significance level will be 0.05 for all hypothesis testing and will be controlled at 5% across any multiple comparisons using appropriate multiple testing procedures. Two-sided tests for superiority will be used throughout.

For the statistical analysis of clinical course, unstageable injuries will be assigned a score of 3 (equivalent to stage III injuries). If a patient experiences multiple sacral/ischial pressure injury simultaneously, the most severe injury will be used for analysis.

#### Primary outcome

The primary outcome will be sacral and ischial pressure injury assessed with the SPI instrument score (range 0–4) over time. For the statistical analysis of clinical course, unstageable injuries will be assigned a score of 3 (equivalent to stage III injuries). For ulcers that progress to deep tissue injuries (DTI), these will be assigned a score of the previous ulcer stage plus one. If a patient experiences multiple sacral/ischial pressure injury simultaneously, the most severe injury will be used for analysis. The primary outcome will be based on the combined stage 1 and stage 2 ulcer types.

Patients will be assessed twice daily by the bedside nurse for pressure injury location and stage from study entry to discharge from the hospital or at least 30 days, whichever comes first. This is a standard wound care evaluation protocol for nursing. Wound care nursing specialist consultation staging will be used instead of bedside nursing staging should a discrepancy occur. If SPI scores are available after discharge and within the 30 days, those data will be included in the analyses as well, even if the SPI are healed or at the worst stage.

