#### Primary outcome analyses

We will assess the efficacy of an IES system added to the standard care versus standard wound care on sacral and ischial pressure injury scores measured over time using a generalized mixed effects ordinal regression cumulative logit model which considers treatment and time (categorical) as fixed effects and subject as a random effect and accounts for (1) the ordinal nature of the data and (2) the within-subject correlation over time. The model will allow differing number of measurements and lengths of follow-up for patients but will assume that shorter follow-up or dropout is largely at random and not due to either improvement or worsening of SPI symptoms. We will also assess the treatment-by-time interaction to assess whether the treatment effect is consistent over time. Given a significant interaction, we will assess the treatment effect at various time points, although the primary analysis will be the treatment effect collapsed over time.

Results will be reported as a proportional odds ratio which estimates the odds of an IES-treated patient having a higher (worse) score than a randomly chosen standard care patient. For example, an odds ratio of 0.6 would mean the treatment was associated with an estimated 40% lower odds of an EIS-treated patient having a higher score compared to standard care; correspondingly, a treated patient has a 40% higher odds of having a lower (better) score compared to a standard care patient.

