**C. Patients starting at stage II** ***N***** = 616 fixed (697 with interims)**					
	**0**	**I**	**II**	**III**	**IV**
**Intervention**	**80**	**0**	**17.5**	**2.5**	**0**
**Control**	**70**	**0**	**20**	**5**	**5**

Hypothetical percent in each pressure ulcer score category by treatment arm, for smallest clinically important effects: overall (A), for stage I (B), and stage II (C)

Table 2 gives total sample size for the combined stages in Table 1 (A), varying the number of measurements per subject (10, 20, 40) and varying ICC (0.2, 0.5, 0.8). The ICC is expected to be relatively high, so the recommended minimum sample size is 548 total (274/gp) for the overall treatment effect combining stages 1 and 2. However, since sufficient power is desired for each of the 2 starting strata, stage I and stage II, roughly the same sample size (548) should be achieved for each strata (see Table 2 for stage I and stage II strata). Therefore, a total maximum (accounting for interim analyses) sample size of approximately 1100 patients was recommended for this trial.

**Table 2 Tab2:** Sample size for varying # measurements and ICC. Data = *N* total. Starting with *N* = 668 total observations (Table 1 (A)), what is the required *N* subjects accounting for ICC and expected number of measurements/subject?

Patient sample	*N* measurements per patient	ICC		
		**.2**	**.5**	**.8**
**Combined stages **Table 1** (A) effect**	**10**	*188*	*368*	*548*
	**20**	*162*	*351*	*542*
	**40**	*148*	*344*	*538*
**Stage I start **Table 1** (B) effect**	**10**	174	342	510
	**20**	150	326	504
	**40**	138	318	500
**Stage II start **Table 1** (C) effect**	**10**	196	384	572
	**20**	168	366	564
	**40**	154	358	562

*N* = 668 assumed 1 measurement per patient (Table 1)

*ICC* intraclass correlation

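### The unstageable rule ignores the injury's earlier stage, so a known stage IV injury can drop from 4 to 3 with no evidence of healing; the effect on the primary result is small

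*Protocol article*

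**What the plan says.** The primary outcome is sacral and ischial pressure injury "assessed with the SPI instrument score (range 0–4) over time" (Protocol article, Primary outcome). It is analysed with a mixed-effects cumulative logit model. The odds ratio refers to an IES patient "having a higher (worse) score than a randomly chosen standard care patient" (Primary outcome analyses), so a lower score counts as better.

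The unstageable rule appears twice. Under Primary outcome, "unstageable injuries will be assigned a score of 3 (equivalent to stage III injuries". Under Significance level, "For the statistical analysis of clinical course, unstageable injuries will be assigned a score of 3". Neither statement makes an exception for an injury that already has a higher recorded stage.

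Three neighbouring rules in the Primary outcome section matter here:

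- For ulcers that progress to deep tissue injury, "these will be assigned a score of the previous ulcer stage plus one".
- For several injuries at once, "If a patient experiences multiple sacral/ischial pressure injury simultaneously, the most severe injury will be used for analysis".
- For frequency, "Patients will be assessed twice daily by the bedside nurse for pressure injury location and stage". Staging by a wound care specialist replaces the bedside staging where the two disagree.

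The caption under Table 1 describes its contents as "Hypothetical percent in each pressure ulcer score category by treatment arm". Table 1(A) places 5% of controls and 0% of IES patients at score IV.

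**The concern.** An unstageable record says that no stage could be assigned at that reading. It does not show that the injury is now less severe than when it was last staged. For an injury never staged above III, a score of 3 is a workable convention. For an injury already staged IV, it discards information on file and records an improvement of one category. If the injury is later staged IV again, the score returns to 4. With two readings a day, both changes can enter the repeated-measures data although nothing has been shown to change in the wound.

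The plan is also uneven. It refers back to the earlier stage for deep tissue injury but not for unstageable injury, although the earlier stage will normally be on record for both.

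What is at stake is the correctness of the worst end of the primary scale: how many readings are shown at III and at IV, and whether severe injuries appear to improve when they have not been shown to.

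**Working it through.** **Step 1. Does any other rule prevent the drop from 4 to 3?**

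- The most-severe rule compares injuries present at the same time. It is not a worst-so-far rule, so it does not hold a single injury at 4.
- Specialist staging applies only where there is a discrepancy, and a specialist may also record the injury as unstageable.
- Multiple imputation (Missing data methods) is for missing values. An unstageable reading is not missing, because the rule gives it a value.

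None of them does.

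**Step 2. Who can be affected?** Any patient with a sacral or ischial injury scored IV. Table 1(A) expects some controls to reach IV. The Trial population section also admits patients with further, higher-stage injuries provided one sacral or ischial injury is stage 1 or 2. Where such an injury is itself sacral or ischial, the most-severe rule makes it drive the score from entry, in either arm.

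**Step 3. Reproduce the plan's own figure.** Inputs from Table 1(A), scores 0 to IV: IES 82.5 / 2.5 / 12.5 / 2.5 / 0%; control 72.5 / 2.5 / 15 / 5 / 5%. Two-sided alpha 0.05 and 90% power (Significance level; Sample size considerations).

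Mann-Whitney probability θ = P(control worse) + ½P(tie):

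0.725×0.4125 + 0.025×0.8375 + 0.15×0.9125 + 0.05×0.9875 + 0.05×1 = 0.5562.

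Noether's formula with tie correction, where p̄ is the mean of the two rows:

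N = (1.960 + 1.282)² × (1 − Σp̄³) / [3(θ − 0.5)²] = 10.507 × 0.5318 / (3 × 0.05625²) = 589.

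The plan states 586. A version with separate null and alternative variances gives 584. The design effect also reproduces: 668 × (1 + 9×0.8)/10 = 547.8, stated as 548.

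**Step 4. Apply the rule.** The documents give no frequency for stage IV becoming unstageable. So let f be the share of control stage IV readings recorded as unstageable, and treat Table 1(A) as true stages. The control row becomes III = 5 + 5f% and IV = 5 − 5f%. The IES row has no stage IV and does not change.

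| f | θ | Odds ratio (worse score, IES vs control) | N |
|---|---|---|---|
| 0 | 0.5562 | 0.526 | 589 |
| 25% | 0.5561 | 0.527 | 592 |
| 50% | 0.5559 | 0.527 | 595 |
| 100% | 0.5556 | 0.529 | 602 |

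Odds ratios are maximum-likelihood proportional-odds fits to the two rows. At f = 100%, N rises by 13/589 = 2.2%. Power at N = 586 goes from about 89.9% to about 89.2%.

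**Step 5. Why the effect is small.** A cumulative logit model on a 0–4 score uses four splits: above 0, above I, above II and above III. Moving readings from IV to III changes only the last. The other three, which hold most of the contrast between arms, are untouched.

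**The case against.** The strongest case against is that the point has almost no consequence for the trial's conclusion. The primary estimate is an odds ratio collapsed over time, and even the extreme case moves it only in the third decimal. No separate stage IV comparison is planned. The rule is prespecified and identical in both arms, and an exception for a rare sequence could sit in a fuller plan. That holds as to size and fixes the point as minor. It does not remove the defect, because the article states the rule twice without condition.

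Two objections to the numbers also stand. Table 1 is headed as scores, so its 5% at IV may already be the result of scoring under this rule; reading it as true stages is an assumption. The shares in the table above are likewise assumed.

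A reader might infer three stronger things that the documents do not support:

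- *That the rule inflates the apparent benefit of IES.* Under Table 1(A), stage IV occurs only in controls, so the false improvement would favour control. It would favour IES only if stage IV injuries became unstageable more often in the IES arm, and nothing in the documents indicates that. Stage IV injuries present at entry would be balanced in expectation.
- *That it costs 8% to 15% of the effect.* The difference in mean score does fall from 0.325 to 0.300 or 0.275 at f = 50% or 100%. But the plan does not analyse a mean score for this outcome.
- *That scores will often swing between 4 and 3.* The documents neither define unstageable nor give its frequency, so this is possible but unquantified.

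**Conclusion.** The scoring gap is real and follows from the text alone: an injury already staged IV and later recorded as unstageable moves from 4 to 3 without evidence of healing, and no other rule stops it. It is a false within-patient improvement that can arise in either arm. On the hypothetical Table 1(A) percentages its net direction is a slight dilution of the IES effect.

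Severity is minor. Over the full range of f, and using the plan's own single-measurement comparison as the yardstick, the primary result and the power barely move. The calculation does not model the repeated readings, and it would understate the number of affected readings if many patients enter with a stage IV sacral or ischial injury. What remains is mainly the split between III and IV in the score distributions that the plan will display over time.

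**What to change.** In both places where the rule stands (Significance level and Primary outcome), replace it with: *An unstageable injury scores the higher of 3 and the last stage recorded for that same injury when it could be staged.* Injuries never staged above III still score 3. An injury known to be stage IV stays at 4 until a stageable reading or healing shows otherwise. This restores the f = 0 row above.

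The cost is one sentence and a programmed carry-forward on staging already collected twice daily; it needs no new visits or patients. There are two drawbacks. Injuries must be linked across readings, which the recorded location allows but which takes some programming because the analysis otherwise keeps only the worst score per time point. And a stage IV injury that truly improved while unstageable keeps a 4 until it can be staged again.
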